### Interim analyses {21b}

There will not be a formal stopping rule for the trial. The investigators do not anticipate problems that are detrimental to participants.

### Methods for additional analyses {20b}

Subgroup analyses will be performed by role on the healthcare team and for prespecified questions about personal and work environment wellness. Mixed model regression analysis will be used.

### Methods in analysis to handle protocol non-adherence and any statistical methods to handle missing data {20c}

Protocol non-adherence is unlikely given that this is a pilot study, and the two psychotherapists leading the intervention designed the protocol, which was based on the sessions they have been hosting for 2 years. Additionally, Death Café debriefing sessions will be randomly attended by other study investigators throughout the course of the study to monitor consistency of adherence to the Death Café intervention structure.

Participants will receive reminders to complete surveys and financial incentives for completion in an effort to acquire a complete dataset. All data will be included in the dataset.

In the event of missing data, this will not be an issue given our use of mixed model regression analysis.

### Plans to give access to the full protocol, participant-level data, and statistical code {31c}

The full protocol and datasets used in this study will be available from the corresponding author on reasonable request.

## Oversight and monitoring

### Composition of the coordinating center and trial steering committee {5d}

The coordinating center is directed by the principal investigators ([name] and JD). All investigators will meet at least monthly to discuss project progress and any unanticipated challenges. There is no separate trial steering committee.

### Composition of the data monitoring committee, its role, and reporting structure {21a}

There is no additional data monitoring committee. The study investigators will monitor the survey data in the REDCap database on a regular basis for any issues and will discuss any that arise at the monthly study team meetings. Any issues that are detected by study investigators must be reported to the principal investigators ([name] and JD) immediately, who will then escalate to the Tulane University Institutional Review Board when appropriate.

### Adverse event reporting and harms {22}

No serious adverse events are anticipated to result from the trial or intervention. If any arise, adverse events will be immediately reported to the Tulane University Institutional Review Board.

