### Intervention description {11a}

In the intervention arm, participants will be asked to participate in at least 4 Death Café debriefing sessions over 3 months hosted by one of our two psychotherapists (RH and NR) [7]. These sessions will occur virtually through a teleconferencing platform in the early evening (after daytime work hours) in an effort to optimize attendance. Subjects will be notified of the date, time, location, and what to expect in the session in advance via the contact information provided on their consent form.

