### Provisions for post-trial care {30}

If subjects experience distress, they can contact the trained psychotherapists on our study team (RH and NR) for triage to appropriate mental health care. Their contact information will be provided to subjects in the consent document. For acute suicidal emergencies, participants will consent to a plan to call 9-1-1 or present to the nearest emergency room.

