### Outcomes {12}

The primary outcome of the study is employee burnout as measured by the Maslach Burnout Inventory (MBI) Score*.* Mean total MBI score and mean subscores will be calculated. Presence of burnout is defined by high values of depersonalization (> 10/30) and emotional exhaustion (> 27/54) with low values for personal accomplishment (< 33/48) as defined in previous studies [40].

Secondary outcomes include employee depression and employee anxiety. These will be determined by the Patient Health Questionnaire 8 (PHQ-8) and Generalized Anxiety Disorder 7-item scale (GAD-7) which evaluate frequency of symptoms over the last 2 weeks. Scores of 10 or higher on these assessments are considered to indicate clinically significant depression or anxiety, respectively [41–43].

Scores will be compared between groups and analyzed from the beginning to the end of the intervention period (at enrollment, 1 month, 3 months, and 6 months after enrollment). The surveys will also include free text response options allowing participants in the intervention arm to comment on strengths and areas for improvement of the intervention.

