### Participant timeline {13}

Subjects in the Death Café arm of the study will participate in 4 debriefing sessions over 3 months from the time of enrollment. Surveys will be administered by email to participants in both arms of the study prior to the intervention, at 1 month, at 3 months, and at 6 months after enrollment. Figures 1 and 2 demonstrate the flow of participants through the study.

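### Adverse events are captured passively and by routes that differ between arms, so spontaneous event counts, or their absence, should not be compared by arm or read as evidence of safety

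*Protocol article*

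**What the plan says.** The section on adverse event reporting and harms {22} gives an expectation and one operative rule: "No serious adverse events are anticipated to result from the trial or intervention. If any arise, adverse events will be immediately reported", the recipient being the institutional review board. It describes no question put to participants and no method common to both arms. Interim analyses {21b} adds "The investigators do not anticipate problems that are detrimental to participants".

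Other sections describe the settings in which an event could surface.

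- **Death Café arm only.** Under Intervention description {11a}, "participants will be asked to participate in at least 4 Death Café debriefing sessions over 3 months hosted by one of our two psychotherapists". Under Strategies to improve adherence {11c}, other investigators sit in on sessions at random. Under Outcomes {12}, the surveys carry "free text response options allowing participants in the intervention arm to comment on strengths and areas for improvement of the intervention".
- **Both arms.** Under Provisions for post-trial care {30}, "If subjects experience distress, they can contact the trained psychotherapists on our study team", and "Their contact information will be provided to subjects in the consent document". Under the data monitoring committee heading {21a}, investigators regularly look through the REDCap survey data for problems and pass these to the principal investigators. No trigger is named.

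The symptom scales are common to both arms. Participant timeline {13} states "Surveys will be administered by email to participants in both arms of the study prior to the intervention, at 1 month, at 3 months"; a last survey follows at month 6. Outcomes {12} gives PHQ-8 and GAD-7 a 2-week look-back and a cut-off of 10. Statistical methods {20a} compares scores between the groups.

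**The concern.** The sessions deal with death, grief and distressing events, and section {30} itself provides for participants who become distressed. Some distress provoked by a session is therefore a plausible adverse effect of this intervention.

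Under a rule that acts only when an event happens to surface, the number reported depends on how often someone is placed to notice. That differs by arm by design. An excess of reports in the Death Café arm could be no more than closer observation. An absence of reports would say little, because nobody is asked. The Implications section suggests that hospital systems consider adopting Death Cafés if they prove effective, so readers will want to know about harm. What was not collected cannot be recovered at analysis.

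**Working it through.** The article gives no adverse event figure to reproduce. The check compares the routes, then asks what the common scales can and cannot supply.

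**1. Opportunities to observe.** Target enrollment is 200 (Sample size {14}) at 1:1 (Trial design {8}), so 100 per arm. At the minimum of 4 sessions, 100 × 4 = 400 person-sessions in the Death Café arm and 0 in the control arm. These are occasions on which distress might be seen. The article does not say that facilitators ask about or record it.

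**2. Why unequal routes matter.** Expected reports in an arm = n × true event rate × probability that an event surfaces. If the true rate is the same in both arms, the expected ratio of reports is simply the ratio of the two surfacing probabilities. The documents give neither, so the following values are assumptions: true rate 10% in both arms, 80% surfacing in the Death Café arm.

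| Control surfacing (assumed) | Reports, Death Café vs control | Ratio |
|---|---|---|
| 80% | 8 vs 8 | 1.0 |
| 50% | 8 vs 5 | 1.6 |
| 20% | 8 vs 2 | 4.0 |

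A true rate of 20% doubles the counts and leaves the ratios unchanged. Only the mechanism should be taken from this, not a value.

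**3. What PHQ-8 and GAD-7 can show.** They are measured identically in both arms, so a sustained rise in symptoms is detectable. For the proportion scoring 10 or higher, with n = 100 per arm, full follow-up and two-sided alpha 0.05,

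power = Φ{[√n·(p₁ − p₀) − 1.96·√(2p̄(1 − p̄))] / √(p₀(1 − p₀) + p₁(1 − p₁))}, where p̄ = (p₀ + p₁)/2.

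For p₀ = 0.10 and p₁ = 0.25: (1.50 − 1.053)/0.527 = 0.848, so power is 0.80. The corresponding increases at 80% power are 20% to about 38% and 30% to about 49%. The base rates are assumed. On the dichotomised scale the trial can therefore show a large increase but not a modest one.

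**4. What the scales can miss.**

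- *Brief distress.* Three follow-up surveys × 2 weeks = 6 weeks out of about 26, or 23%. Within the roughly 13 weeks of sessions, the 1- and 3-month surveys cover 2 × 2 = 4 weeks, or 31%. Distress that settles within days of a session will often fall outside these windows.
- *A minority who worsen.* If U participants in an arm cross the cut-off upward and D cross downward, the change in prevalence is (U − D)/n. Any U and D with the same difference give the same result, so U is not visible. A comparison of mean scores hides it in the same way. No count of upward crossings is described.

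**The case against.** The strongest objection is that this is a condensed article. Event definitions, forms and procedures are commonly left to the full protocol, and their absence here is not a fault. That is accepted. The point rests instead on what the article does state: a rule that waits for events to arise, alongside contact and free text placed in one arm.

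Second, no between-arm count of adverse events is planned; {22} is a duty to report to the review board. This is also correct. The point is therefore a limit on how reported events, or their absence, may be read, not an error in a specified analysis. Similarly, the free text asks for feedback on the intervention and is not a harms question. It matters only as one more place where a complaint could surface in one arm.

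Third, the trial is described as a pilot ahead of a definitive study. That lowers the stakes, but a pilot is a natural place to start collecting harms evenly.

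A reader might also infer several stronger things that the documents do not support:

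- *That the trial cannot show whether debriefing causes distress.* PHQ-8, GAD-7 and the burnout inventory are collected on one schedule in both arms and compared, and a difference can go either way.
- *That controls have no route beyond telephoning the psychotherapists.* Section {30} speaks of contact in general and gives the details to all subjects, and the survey review in {21a} is not restricted by arm.
- *That a particular multiple of excess reports is to be expected.* Any multiple depends on surfacing probabilities that nobody has estimated, and equal surfacing gives a ratio of 1.0.
- *That not anticipating serious events contradicts having a plan for distress and emergencies.* Providing for an unlikely event is ordinary prudence, and that wording need not change.

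**Conclusion.** The point holds as a limit on inference about harm. Spontaneously surfaced events are ascertained unequally: about 400 person-sessions against none at minimum attendance, assuming 100 per arm and everyone attending 4. Counts of such events, including zero, should not be compared between arms or presented as evidence of safety.

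The trial keeps a sound randomized comparison of sustained symptoms through PHQ-8 and GAD-7. Two gaps remain: brief session-related distress, since the look-backs cover about 23% of follow-up if surveys are answered on schedule, and individual worsening hidden in a net comparison. How far surfacing really differs between the arms cannot be derived from the article, so the size of any bias is unknown. Nothing here affects the primary burnout comparison. This is a worthwhile, inexpensive improvement rather than a threat to the trial's main result.

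**What to change.** In {12} and {22}:

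1. Add one identical item to the existing REDCap surveys at 1, 3 and 6 months in both arms. It should ask about any distress or need for mental-health help since the last survey, and whether the participant felt this was related to the study. Report it by arm. Because participants know their allocation, base the between-arm comparison on whether distress or need for help occurred, and treat the perceived relation as descriptive.
2. List events disclosed in sessions or by direct contact separately, outside any between-arm count. Reporting to the review board is unaffected.
3. Tabulate by arm, at each follow-up, the number moving from below 10 at baseline to 10 or higher on PHQ-8 or GAD-7. The denominator is those below 10 at baseline with a score at that survey.

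The cost is slightly longer surveys and one extra descriptive table. The item needs to be in place before the first 1-month survey is sent, since it cannot be reconstructed later.

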### Frequency and plans for auditing trial conduct {23}

Monthly study team meetings will be hosted as above to continuously evaluate the trial conduct. The Tulane University Institutional Review Board and funding source (Spirit of Charity Foundation) require annual reports. No other audits will be performed, unless requested by the study sponsor, funding source, or Tulane University Institutional Review Board.

### Plans for communicating important protocol amendments to relevant parties {25}

Any protocol amendments will have to be approved by the Tulane University Institutional Review Board and the hospital-based Research Review Committee. They will also have to be updated on clinicaltrials.gov and communicated to the study funder and sponsor.

### Dissemination plans {31a}

The findings of the trial will be presented at local and national or international scientific meetings. The authors also plan to publish the results of this trial in peer-reviewed journals.

## Discussion

### Implications

Burnout is a substantial problem among ICU clinicians and interventions to prevent or reduce burnout are sparse [5, 15, 29]. Identification of interventions that can prevent burnout in physicians and staff caring for critically ill patients is vital. STOPTHEBURN is the first study to evaluate the efficacy of the hospital-based Death Café to prevent burnout in ICU clinicians. Additionally, the virtual platform by which this study is proposed also provides a novel venue that may increase dissemination to in-need critical care providers dealing with COVID-19 worldwide. If this intervention is feasible and effective in this pilot study, a future, multicenter definitive clinical trial will be undertaken. Reducing burnout in ICU healthcare clinicians has the potential to increase satisfaction/engagement with work, reduce healthcare provider turn over, and improve the quality of care provided to patients. If effective, hospital systems should consider implementing Death Cafés to reduce burnout among ICU clinicians.

### Challenges

While we aim to recruit a sample which represents all ICU employees, participants with burnout, depression, and anxiety symptoms may be difficult to engage in a research study. Feeling already overwhelmed, the employees most at risk may not engage with a time-consuming intervention, which could lead to underestimation of the intervention’s effect. We will do our best to increase subject participation by making participation in the study as convenient as possible using virtual platforms and by providing monetary reimbursement for the time participants spend completing surveys and participating in Death Café sessions.

We recognize that our intervention may have differential impact based on a number of factors. It is possible that burnout may vary at different times of the year with busier times leading to higher rates of burnout. The COVID-19 pandemic may increase the level of burnout and also limit the availability of those most in need to seek help. Certain demographic factors (marital status, having children, etc.), factors related to personal wellness (sleep, history of depression or anxiety, etc.), and those related to work environment (recent conflicts or deaths, etc.) may also play a role. We will not specifically recruit participants based on these factors, as our randomized controlled trial structure will help to account for these and other potential confounders. We will be performing multivariate regression analyses and other subgroup analyses to help us to evaluate these relationships. We hope to identify the employee subpopulations who benefit the most from Death Café debriefing sessions.

The COVID-19 pandemic has limited options for hosting in-person Death Cafés due to the need for social distancing and limiting gatherings to less than 10 participants. As a result, Death Café interventions will be adapted to an online format via a virtual platform such as Zoom. We suspect the virtual modality will make it easier for participants to attend and affiliate outside the workplace environment. Death Cafés are traditionally in-person gatherings, so transition to virtual meetings is a departure from the norm. There is concern that moving to an online platform may lead to a reduction in therapeutic efficacy given that in-person interaction is believed to be a fundamental feature of Death Cafés. Given the need to adapt to virtual social gatherings in the wake of COVID-19, many are now more comfortable with this modality and even expect this platform to serve as an appropriate social milieu for larger gatherings. That said, participation in Death Cafés from home may limit participants’ ability to share stories if they do not perceive strict confidentiality in their home setting (i.e., proximity of family members), and the virtual setting may introduce other confounders (distractions, technological difficulties, etc.). Virtual Death Cafés are arising in the community de novo, and thus, we aim to adapt our intervention to what we see as an emerging trend.

## Trial status

Trial enrollment will begin July 1, 2020, at UMC and is anticipated to conclude July 1, 2021. The current study protocol is dated May 4, 2020.

## Data Availability

The datasets used and/or analyzed during the current study will be available from the corresponding author on reasonable request.

## Abbreviations

GAD-7: Generalized Anxiety Disorder 7-item scale
ICU: Intensive care unit
PHQ-8: Patient Health Questionnaire 8
MBI: Maslach Burnout Inventory
